## Abstract

**Background:**

HIV incidence has recently increased among people who inject drugs (PWID) across the United States, with outbreaks occurring in states with long-standing syringe service programs (SSPs) including Massachusetts (MA). Antiretroviral pre-exposure prophylaxis (PrEP) is an evidence-based HIV prevention strategy recommended for PWID, but uptake in this marginalized population is extraordinarily low.

**Methods:**

We describe the design and procedures for a National Institute on Drug Abuse (NIDA)-funded (R01) randomized controlled trial (RCT) testing the efficacy of “PrEP for Health,” a multicomponent behavioral intervention to increase PrEP uptake, adherence, and persistence among HIV-negative PWID attending SSPs in two areas of the U.S. Northeast that are heavily affected by injection-related HIV transmission. Participants are equally randomized to receive the “PrEP for Health” intervention (involving individually tailored HIV and PrEP education, motivational interviewing, problem-solving skills and planning, and ongoing navigation support) or an enhanced standard of care (eSOC) control condition involving a brief educational video on the utility of PrEP for HIV prevention. Co-primary outcomes are PrEP uptake (using medical/pharmacy records) and adherence (using tenofovir quantification in hair samples); a secondary outcome is PrEP persistence (using medical/pharmacy records) over 12 months. Major assessments occur at baseline, 1-, 3-, 6-, and 12-month follow-up visits. Planned analyses will examine intervention efficacy, specific hypothesized conceptual mediators of the intervention effect (e.g., self-perceived HIV risk; PrEP knowledge, interest in use, motivation, and behavioral skills) and epidemiologically linked moderators (e.g., age; gender; condomless vaginal or anal sex).

**Discussion:**

Findings from our extensive preliminary research with the study population revealed that a multicomponent, theory-based intervention targeting PrEP knowledge, motivation, self-efficacy, behavioral skills, and structural barriers to PrEP access is urgently needed for PWID who are at risk of HIV acquisition. We also learned that SSPs represent a highly acceptable service setting for delivering such interventions. In this study, we are evaluating the efficacy of the “PrEP for Health” intervention. If efficacious, findings from our implementation evaluation could help guide its dissemination to diverse SSPs and possibly other community-based settings accessed by this population.

**Trial registration:**

ClinicalTrials.gov number NCT04430257, registered June 12, 2020.

## Background

In the context of the ongoing opioid and polysubstance use crises in the United States, Human Immunodeficiency Virus (HIV) transmission among people who inject drugs (PWID) is a critical public health challenge [1, 2]. Increases in HIV incidence have recently been detected in this population after declining for decades, [3, 4] and concentrated HIV outbreaks among PWID have occurred in diverse U.S. regions, including areas with syringe service programs (SSPs) and other established HIV prevention services [5–19]. In Massachusetts (MA), a large HIV outbreak among PWID in two communities (Lawrence and Lowell, MA) from 2015 to 2018 appeared to be connected to increasing use of fentanyl (which increases injection frequency and receptive syringe sharing) and stimulants (which may increase sexual and injection-related exposures to HIV) [5, 7]. In addition to these behavioral factors, limited engagement in HIV prevention and treatment services due to low self-perceived HIV risk and structural factors that disrupt healthcare utilization (e.g., homelessness and incarceration) likely also contributed [5, 20]. Since 2018, additional clusters of incident HIV infections have been identified among PWID in Boston and other MA cities, [21] which may have worsened during the COVID-19 pandemic [22].

Antiretroviral pre-exposure prophylaxis (PrEP) is an evidence-based HIV prevention strategy that is recommended for PWID at risk of HIV acquisition, [23] yet PrEP research and actual uptake among PWID has been dismally low despite high potential for clinical benefit [24]. For example, in a survey of 423 PWID in the Greater Boston Area, 92% self-reported injection and sexual behaviors aligned with clinical indications for PrEP, but < 2% had ever used PrEP [25]. Our formative qualitative research in this region attributed low PrEP uptake among PWID to low self-perceived HIV risk, suboptimal PrEP knowledge and interest, [26] and multilevel barriers to accessing PrEP in clinical settings including pervasive stigma against PWID in healthcare systems [27, 28]. Nationally, PrEP prescribers’ limited willingness to prescribe PrEP to PWID may also limit uptake.[26, 29−31] While innovative low-barrier PrEP services have been implemented for PWID experiencing homelessness in Boston [32] and several other cities, [33, 34] evaluation research has highlighted significant challenges with PrEP adherence and persistence among PWID, [34, 35] underscoring the need for multicomponent behavioral interventions that target multiple hypothesized determinants of PrEP access and adherence [27, 36].

As PWID may have limited or ineffective interactions with traditional healthcare systems, [28, 37, 38] alternative, community-based and culturally-tailored settings may provide a more effective setting for PWID to access PrEP. Syringe service programs (SSPs), where staff routinely provide PWID with health information and support, [27, 28, 34, 37, 39−41] are highly acceptable venues for PrEP interventions for PWID, whether PrEP can be delivered onsite or through supported referrals to local, trusted clinics [34]. In our formative research, SSP staff in MA perceived PrEP to be aligned with their organizational missions and viewed PrEP integration into their existing services as acceptable and feasible [42]. Some SSPs already provide PrEP information and initial screening services (e.g., HIV testing), [43, 44] and SSP-based interventions that support adherence to medications for the treatment of Hepatitis C Virus (HCV) and opioid use disorder have been successful [45–47]. Given the growing numbers of SSPs nationally, [48] these venues have high potential for increasing PrEP uptake, adherence, and persistence among PWID.

Social Cognitive Theory (SCT) provides a valuable theoretical basis for behavioral interventions targeting the multilevel barriers to PrEP uptake, adherence, and persistence for PWID. SCT posits that people, their behaviors, and surrounding environments interact to influence how and when behaviors are performed, [49] with a focus on cognitions (i.e., knowledge), motivations, [50] self-efficacy, and behavioral skills and strategies for overcoming environmental (i.e., structural) barriers [51, 52]. SCT has proven useful in interventions supporting antiretroviral uptake and adherence (for HIV treatment and prevention) in at-risk, socially marginalized populations, including among those who use substances [53, 54]. Individually tailored education, motivational interviewing (MI), and problem-solving and planning are key SCT-informed strategies that could support PrEP uptake, adherence, and persistence among PWID if sufficient structural supports are also provided [55–58].

Patient navigation is an evidence-based, patient-centered healthcare delivery strategy that provides individually tailored supports to help people overcome barriers to accessing and staying engaged in healthcare services [59]. Patient navigation strategies have successfully improved HIV, HCV, and chronic disease care [59, 60]. Many of the activities included in these interventions (e.g., facilitating referrals and appointments, planning for transportation, [61] providing emotional support) could help address multilevel barriers to PrEP uptake among PWID, [26, 27] and patient navigators can also be trained to work successfully with marginalized populations (e.g., by avoiding stigmatizing language) [62–65]. As patient navigation alone may be insufficient in targeting all barriers to PrEP uptake and longer-term adherence and persistence, [66, 67] we hypothesized that a multicomponent intervention combining patient navigation with SCT-informed behavioral intervention strategies (individually tailored education, MI, problem-solving and planning) could effectively support PrEP uptake and develop a foundation of knowledge and skills upon which individuals’ longer-term PrEP adherence and persistence could be built [40, 68]. We thus developed the brief, multicomponent “PrEP for Health” behavioral intervention—delivered by trained PrEP patient navigators within SSPs—to improve PrEP uptake and adherence (co-primary outcomes) and persistence (secondary outcome) among PWID at risk of HIV acquisition. In this paper, following the Standard Protocol Items: Recommendations for Interventional Trials (SPIRIT) Statement [75], we detail the procedures for a randomized controlled trial (RCT) testing the efficacy of PrEP for Health within two SSPs in MA.

## Methods

### Overview of study design

PrEP for Health is a two-arm RCT aiming to enroll 200 HIV-negative PWID attending two SSPs in MA (n = 100 per site). Based on the locations of recent HIV outbreaks and clusters among PWID, we partnered with two SSPs (i.e., study sites) in Lawrence and Boston/Cambridge, MA, jurisdictions heavily affected by opioid and stimulant use and injection-related HIV transmission. The SPIRIT figure of this trial, including the schedule of screening, enrollment and follow up visits, is illustrated in Fig. 1. In brief, participants are randomized 1:1 to receive the PrEP for Health intervention or an enhanced standard of care (eSOC) control condition, as detailed below. Participants are then followed for 12 months with major assessment visits scheduled at baseline and 1-, 3-, 6-, and 12-month follow-up timepoints. Participants receive escalating incentives across these assessment visits (ranging from $20-$50). Participants randomized to the PrEP for Health intervention also receive $10 for each of two primary intervention sessions. Participants provide written informed consent (described below). All study materials described in the sections below are available in English and Spanish (following professional translation and verification by bilingual research personnel). The Fenway Health institutional review board (IRB) reviewed and approved all study protocols. The following description of the protocol is based on Version 1.7, most recently updated and approved on 10/26/2022.

**Fig. 1 Fig1:**
[figure not shown]
SPIRIT figure for the PrEP for Health trial

### Participant recruitment and screening

Participant recruitment involves active and passive methods. At each SSP, research team members (including research assistants, project manager, and navigators) and SSP personnel (including program managers and outreach specialists) approach potential participants seeking SSP services to briefly describe the study and assess interest in participating. At both study sites, screening is integrated into standard SSP intake processes to facilitate efficiency and reduce participant burden. Active recruitment also occurs when research staff accompany SSP personnel during wider community outreach (e.g., via mobile outreach to streets, parks, homeless encampments, shelters, and other local service organizations). Passive recruitment involves posting flyers and sharing business cards at the SSPs, nearby health centers, substance use treatment facilities, churches, and other places where PWID congregate. Recruitment is currently ongoing.

With support from SSP personnel, who often know potentially eligible members of the target population and can refer them to the study, research staff conduct brief eligibility screenings. Detailed eligibility criteria are described in Table 1. In brief, eligible individuals are ≥ 18 years old; self-report injection of drugs for non-medical reasons in the past month; and are HIV-uninfected (confirmed using a rapid HIV screening test or enzyme-linked immunosorbent assay; ELISA). Individuals may enroll in the study prior to confirmation of HIV serostatus but are withdrawn if test results indicate HIV-positive serostatus. Anyone receiving a positive HIV test result is referred to HIV care through standard processes at each SSP.

**Table 1 Tab1:** Eligibility Criteria for the PrEP for Health trial

Inclusion	Exclusion
• Age 18 and older	• Does not understand and speak English or Spanish
• Any drug injection, past 30 days	• Unable to provide informed consent due to severe mental or physical illness, cognitive impairment, or substance intoxication at the time of enrollment
• Any HIV risk behavior, past 30 days ○ Receptive syringe sharing ○ Engagement in transactional sex ○ Any condomless sex	• HIV positive, confirmed by enzyme-linked immunosorbent assay (ELISA) testing already available at each SSP or by FDA-approved rapid HIV Antibody test if blood draws are unsuccessful
• Never used PrEP, or discontinued PrEP more than 6 months ago	

### Informed consent and enrollment

After confirming eligibility, trained study staff either conduct informed consent immediately or schedule an appointment for a later date, depending on participant preference. Study staff conduct informed consent in a private room using a consent document written according to Federal standards at or below an eighth-grade reading level that describes the study rationale, procedures, risks, benefits, measures to protect confidentiality, and participants’ rights and responsibilities. After explaining all study procedures, study staff then answer questions and gauge comprehension using a brief, structured assessment. Individuals who consent to participate sign the informed consent form, which is reviewed by the Site PI or their designees.

### Randomization

Following baseline assessments (see Fig. 1 and Measures section below for details), participants are randomized into either of the two study arms using a pre-programmed randomization module in REDCap. Randomization is site-specific to ensure balance within site. After randomization, participants randomized to the PrEP for Health intervention condition can elect to have their initial intervention session with the PrEP Navigator that day or schedule an appointment for a later date.

### Timing of assessments

Research staff administer assessments at baseline (pre-randomization) and 1-, 3-, 6-, and 12-month follow-up visits (post-randomization). Assessments are not blinded, however only research staff uninvolved in intervention delivery administer follow-up assessments to reduce social desirability bias. Moreover, study staff use standardized survey instruments and are instructed in how to mitigate bias in survey administration. Between 6- and 12-month assessments, check-ins (by phone or in-person) are incentivized ($10/check-in) to update locator information, support retention, and facilitate ongoing communication between major assessments.

### PrEP for Health Intervention condition

PrEP for Health is a two-session, manualized, multicomponent intervention grounded in SCT and informed by prior interventions with similar populations. Given that a key strategy is MI, draft manuals were reviewed and refined by a certified Motivational Interviewing Network of Trainers (MINT) trainer. The intervention is delivered by trained PrEP Navigators through up to two in-person intervention sessions at SSP study sites, followed by ongoing navigation support for a period of three months. The two in-person intervention sessions cover PrEP uptake (i.e., “Module 1,” which may be repeated during the second intervention session if necessary), and PrEP Adherence and Persistence (i.e., “Module 2”). Navigators are individuals without healthcare training who have personal or professional experience working with PWID (i.e., they are not licensed clinical social workers and no other certifications or licenses are required).

Interventionist training and supervision: PrEP Navigators receive extensive training in the intervention manual content (including detailed background information on HIV transmission and PrEP); MI (involving an initial 8 h of self-paced web-based training); principles of harm reduction (including overdose prevention), cultural humility, and trauma-informed services; problem-solving and de-escalation techniques; and research ethics. An MI-experienced licensed clinical social worker conducts ongoing supervision and training to enhance intervention delivery and ensure fidelity to the intervention manual and principles of MI.

Module 1: PrEP uptake: In the first in-person intervention session, PrEP Navigators use specific strategies to deliver individually tailored HIV and PrEP education and MI to address HIV risk perceptions and increase PrEP interest and motivation. PrEP Navigators also use this session and ongoing follow-up interactions (described below) to engage participants in problem-solving and planning to build their self-efficacy and behavioral skills to facilitate the process of obtaining initial PrEP screening and prescriptions. PrEP Navigators use patient navigation techniques to assess barriers to PrEP uptake, navigate the PrEP medical care system (e.g., through supported referrals to SSP-based or other local prescribers familiar with healthcare for PWID), and engage participants in problem-solving and planning around anticipated challenges in obtaining PrEP prescriptions (e.g., overcoming insurance or copay barriers). If participants do not initiate PrEP within one month of this initial intervention session, this PrEP uptake-focused content (i.e., Module 1) can be repeated in participants’ second intervention session to help trouble-shoot around initial uptake.

Module 2: PrEP adherence and persistence: For participants who initiate PrEP, in the second in-person intervention session, PrEP Navigators use similar strategies described above (e.g., MI, patient navigation techniques, problem-solving and planning) to motivate and support participants in achieving optimal PrEP adherence and persistence. This includes problem-solving around adherence challenges and anticipated adherence facilitators informed by evidence-based interventions and formative research (i.e., specific “steps” towards optimal adherence such as planning for transportation to pharmacies and PrEP care appointments). Finally, PrEP Navigators support participants in developing an individually tailored PrEP routine, including planning for future PrEP prescription refills and care appointments, and devising plans for handling missed doses and lapses in PrEP care.

Ongoing PrEP navigation support: For three months after the initial intervention session, PrEP Navigators provide additional, ongoing MI and PrEP navigation, as needed, through in-person, phone, and text-based interactions to support participants in coping with ongoing or new challenges with PrEP uptake, adherence, and persistence. Near the end of this three-month period, PrEP Navigators’ help participants plan for ongoing PrEP adherence and persistence.

### Enhanced standard of care control condition

Following randomization, participants in both the PrEP for Health intervention and eSOC control conditions watch a brief educational video on PrEP that was adapted by our research team from existing resources (e.g., whatisprep.org). The video is available in English and Spanish and uses non-technical terminology to describe what PrEP is and how it works to prevent HIV via sexual and injection exposures. Additionally, all participants, regardless of study condition, are eligible to receive any services offered at the local SSP study sites, which includes referrals to local PrEP clinicians and other healthcare providers. Moreover, participants who attend local PrEP clinics and are deemed clinically eligible for PrEP may be prescribed PrEP according to standard clinical practices.

### Measures

At all major assessment visits, participants complete interviewer-administered assessments of HIV and PrEP knowledge, perceived HIV risk, PrEP interest and self-efficacy, and patterns of substance use, sexual behaviors, physical and psychosocial health conditions, and health service utilization. Socio-demographics (e.g., race/ethnicity, age) are assessed at baseline only. Medical record review is conducted throughout the course of the study. Biological measures of adherence to oral PrEP (i.e., concentrations of tenofovir in hair samples [70, 71]) are collected at 3-, 6- and 12-month follow-up visits only, and incident HIV infection is assessed at 12-month follow-up visits only (Table 1). Because a long-acting injectable PrEP medication has recently been approved for prescribing among people who have sexual exposures to HIV, [71–74] some participants might use this newer formulation instead of oral PrEP medications. For participants who use injectable PrEP, which must be administered by a healthcare professional, we will track adherence using medical and pharmacy records, as biomarkers of adherence to injectable PrEP are not available and may not provide additional information on adherence beyond review of medical and pharmacy records.

Co-primary outcome measures: Our first co-primary outcome, PrEP uptake, is primarily assessed via visual confirmation that a PrEP prescription was filled and received. At each follow-up assessment, we also request that participants bring in their PrEP prescription packaging to confirm that the prescription was picked up. For injectable PrEP, uptake will be defined as receipt of their first injection,

Our second co-primary outcome, PrEP adherence, is assessed only among those who report initiating PrEP (i.e. taking at least one pill or receiving at least one injection). We assess adherence at 3-, 6-, and 12-month follow-up visits by collecting hair samples to test for the presence of detectable levels of tenofovir, which reflect adherence to either tenofovir disoproxil (TDF) or tenofovir alafenamide (TAF) over approximately the prior month. Samples are ~ 50–100, 1-2 mm-long strands of hair cut with scissors. Samples will be analyzed at the University of California, San Francisco, Hair Analysis Lab for quantification of tenofovir levels [69]. We supplement this biological monitoring with self-reported adherence at all major assessment visits. For injectable PrEP, which involves a monthly intragluteal injection for one month and then bimonthly injections thereafter, optimal adherence will be defined as receipt of injections within one month of their target injection date, which is the time at which people would need to reinitiate monthly injections for two injections (i.e., reload) due to waning drug levels.

Secondary outcome: We assess our secondary outcome, PrEP persistence, using pharmacy and medical records to confirm prescription refill maintenance and attendance at PrEP care follow-up visits. PrEP persistence will be defined as having ≥ 16 days of oral PrEP medication filled per 30-day period, or receiving PrEP injections within one month of their target dates, for at least three-quarters of the months since initiation to study completion (approximately 9/12 months) [76].

Conceptual mediators: Informed by our preliminary studies, conceptual mediators of intervention effects are measured by self-report at each major assessment visit and include HIV knowledge (assessed using selected and adapted items from the International AIDS Questionnaire [78] and the Marsch HIV/AIDS knowledge test [78, 79]), perceived HIV risk (using items adapted from the validated Perceived Risk of HIV Scale [80]), and PrEP knowledge, interest, motivation, and behavioral skills (using items adapted from research with people who use drugs [81]). PrEP use intentions and self-efficacy are measured using selected and adapted items from work by Walsh, [82] and anticipated PrEP stigma from work by Calabrese, et al. [83]. Structural barriers to PrEP access include healthcare access and utilization (items from the National HIV Behavioral Surveillance Survey [84]) and stigma from medical providers (from Fong, et al. [85]).

Epidemiologically linked moderators: Also based on our formative research, we hypothesize observing heterogeneity in intervention effects according to participant age, gender, and baseline sexual risk (specifically, condomless vaginal or anal sex) and polysubstance use (including stimulants), assessed by self-report at baseline and follow-ups assessment visits.

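### For oral PrEP, uptake is counted at a confirmed fill but adherence only among those who report taking a pill, so someone who fills, takes nothing and says so falls outside the adherence comparison

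*Protocol article*

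**What the plan says.** All references are to the protocol article.

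- **Uptake, oral (Measures).** The first co-primary outcome "is primarily assessed via visual confirmation that a PrEP prescription was filled and received". Participants are also asked to "bring in their PrEP prescription packaging to confirm that the prescription was picked up". The Abstract gives the source as records: "Co-primary outcomes are PrEP uptake (using medical/pharmacy records) and adherence (using tenofovir quantification in hair samples". All of these establish that the drug was obtained. None requires that any was taken.
- **Uptake, injectable (Measures).** "For injectable PrEP, uptake will be defined as receipt of their first injection".
- **Adherence (Measures).** The second co-primary outcome "is assessed only among those who report initiating PrEP (i.e. taking at least one pill or receiving at least one injection". For oral PrEP it is measured at 3, 6 and 12 months by "collecting hair samples to test for the presence of detectable levels of tenofovir".
- **Persistence, oral (Measures).** The secondary outcome is also based on fills: "having ≥ 16 days of oral PrEP medication filled per 30-day period", for at least three-quarters of the months since initiation.
- **Blinding (Timing of assessments).** "Assessments are not blinded", although follow-up assessments are given by staff who do not deliver the intervention.
- **Analysis (Statistical analyses).** Uptake is also analyzed by Cox models for time to PrEP initiation. Here initiation stands for the uptake event, while in the adherence definition it means a reported dose. Participants are to be analyzed by intent to treat.

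**The concern.** The adherence set for oral PrEP is not the set of uptake successes. It is chosen after randomization by the participant's own statement, made in an unblinded interview, that at least one pill was taken. Someone who fills the prescription, takes nothing and says so has the most complete form of non-adherence. That person counts as a success on the first co-primary outcome and is not assessed on the second. Fill-based persistence does not detect the non-use either.

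If such people are equally common in both arms, both adherence percentages are too high but the contrast shifts only in scale. If they are more common in one arm, leaving them out favors that arm. The article itself describes frequent loss or theft of medications (Discussion) and difficulty with adherence (Background) in this population, so the group need not be negligible.

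The restriction applies to who is assessed, not only to who is analyzed. By the article's account, hair reflects roughly the prior month, so a sample not requested at a visit cannot be replaced by one taken much later.

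**Working it through.** **1. The plan's own figure.** Inputs from Sample size calculations: uptake 25% v 50%, 80 completers per arm, two-sided alpha 0.05, 20% attrition.

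- Null SE = sqrt(2 × 0.375 × 0.625 / 80) = 0.0766. Alternative SE = sqrt((0.25 × 0.75 + 0.50 × 0.50) / 80) = 0.0740.
- Power = Φ((0.25 − 1.96 × 0.0766) / 0.0740) = 0.912, against the stated 90%.
- Enrollment = 80 / (1 − 0.20) = 100 per arm, 200 in all, as stated.

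The uptake sizing reproduces, and this point does not change it.

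**2. Where each kind of participant falls (oral PrEP, as written).**

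| Participant | Uptake | Adherence |
|---|---|---|
| Fills, takes pills, reports it | success | in the set, hair-tested |
| Fills, takes none, reports a pill | success | in the set, hair can show no drug |
| Fills, takes none, says so | success | not assessed |
| Reports a pill, no confirmed fill | not shown by a fill | in the set |

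The third row is the gap. For injectable PrEP it cannot arise, because uptake and initiation are both the first injection.

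**3. Size, by illustration.** The document gives neither a never-take share nor an adherence rate, so both are assumed. Expected fills among completers: 80 × 0.50 = 40 (intervention) and 80 × 0.25 = 20 (control). Let *a* be adherence among takers, set at 50% in both arms, and *f* the share of fillers who take nothing and say so.

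- Written rule: adherence = *a*, whatever *f* is.
- All fills, never-takers scored non-adherent: adherence = *a* × (1 − *f*).
- Difference over all fills (intervention minus control) = *a* × (*f* control − *f* intervention).

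| *f* interv./control | Never-takers | Written rule | All fills | Difference | All 80 completers |
|---|---|---|---|---|---|
| 0% / 0% | 0 v 0 | 50% v 50% | 50% v 50% | 0 | 25% v 12.5% |
| 15% / 5% | 6 v 1 | 50% v 50% | 42.5% v 47.5% | −5 points | 21.3% v 11.9% |
| 20% / 20% | 8 v 4 | 50% v 50% | 40% v 40% | 0 | 20% v 10% |
| 10% / 30% | 4 v 6 | 50% v 50% | 45% v 35% | +10 points | 22.5% v 8.8% |

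For example, 0.50 × 0.85 = 0.425 and 0.50 × 0.95 = 0.475. Over all completers, 40 × 0.425 / 80 = 0.2125 and 20 × 0.475 / 80 = 0.119.

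**4. Against sampling error.** With 40 v 20 and 50% adherence, SE = sqrt(0.25/40 + 0.25/20) = 0.137, so a 95% interval is about ±27 points.

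**The case against.** A reader might go further and infer that the rule flatters the intervention arm, because navigators help people obtain fills. The document does not support a direction. The same navigators deliver motivational interviewing before uptake, an adherence session for those who start, and three months of support, any of which could lower the never-take share. Pressure to please an interviewer would lead people to claim a pill, which brings them into the set where hair can show no drug. If that pressure were stronger in the intervention arm, it would count against that arm. The 10%/30% row shows the sign reversing.

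A reader might also infer that a never-taker can never be counted as non-adherent. That is true only of oral users who report no dose.

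The reverse mismatch, a reported pill without a confirmed fill, is weaker. Uptake is said to be assessed primarily by visual confirmation, and medical records are reviewed throughout, so other sources may confirm those cases.

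Three further objections carry some weight. The shifts in the table are well inside the sampling error. Scoring detail is often left to an analysis plan, which is not shown. Adherence among those who start a drug is also a recognizable quantity to estimate. However, a shift caused by a definition is bias and does not average out as noise does. The rule on who is assessed is stated here rather than left open. And wanting adherence among starters does not explain why starting means a fill for one co-primary outcome and a self-reported dose for the other.

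**Conclusion.** The mismatch stands for oral PrEP. Fillers who report no dose are uptake successes with no adherence value, and the adherence set depends on an unblinded self-report made after randomization, which sits badly with the stated intent-to-treat comparison. If the never-take share differs by arm, the adherence contrast is biased by the adherence rate among takers times that difference. In the illustrations this runs from −5 to +10 points while the written analysis shows zero. The direction is unknown, and every never-take share and the 50% adherence rate are assumptions. The 40 v 20 fills follow from the plan's uptake rates and completer numbers. Injectable PrEP, and never-takers who claim a pill, are outside the point.

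**What to change.** 1. Define initiation once, for both co-primary outcomes and for the Cox model: a confirmed fill and receipt for oral PrEP, or the first injection.
2. If adherence stays conditional on initiation, make its set everyone who meets that definition.
3. At the 3-, 6- and 12-month visits, request hair from everyone in that set who obtained oral PrEP, and from anyone who reports a pill without a confirmed fill.
4. Score fillers who report no dose as non-adherent.
5. Keep the self-report set as a sensitivity analysis.
6. A fill is itself a post-randomization event, and one the intervention targets, so the new set still does not give a fully randomized comparison. Add a supportive analysis of all randomized participants with non-initiators counted as not adherent.

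The cost is protocol and analysis-plan wording, a few more hair requests at visits that already take place, and a slightly lower adherence percentage. The sample size is unchanged. The article describes recruitment as ongoing, so the hair requests should be changed early.
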